## Abstract

**Background:**

More than 50% of people who die by suicide have not been in contact with formal mental health services. The rate of people who fly ‘under the radar’ of mental health services is higher among men than women, indicating a need to improve engagement strategies targeted towards men who experience suicidal thoughts and/or behaviours. In Australia, a range of mental health support services exist, designed specifically for men, yet, a substantial proportion of men do not use these services. The aim of this study is to evaluate whether a brief online video-based messaging intervention is an effective approach for encouraging men with suicidal thoughts and/or behaviours to engage with existing support services.

**Methods:**

Informed by a literature review, surveys, and consultation with men with a lived experience of suicidal thoughts and/or behaviours, we designed five video-based messages that will be used in this five-arm randomised controlled trial. A total of 380 (76 per arm) men aged 18 years or older with suicidal thoughts who are not currently accessing formal mental health services will be recruited online and randomly assigned to watch one of the five web-based video messages. After viewing the video, men will be presented with information about four existing Australian support services, along with links to these services. The primary outcome will be help-seeking, operationalised as a click on any one of the four support service links, immediately after viewing the video. Secondary outcomes include immediate self-reported help-seeking intentions in addition to self-reported use of the support services during a 1-week follow-up period. We will also use the Discrete Choice Experiment methodology to determine what aspects of support services (e.g. low cost, short appointment wait times) are most valued by this group of men.

**Discussion:**

This study is the first to evaluate the effectiveness of a brief web-based video messaging intervention for promoting engagement with existing support services among men with suicidal thoughts who are not currently receiving formal help. If found to be effective, this would represent a scalable, cost-effective approach to promote help-seeking for this at-risk population. Limitations and strengths of this study design are discussed.

**Supplementary Information:**

The online version contains supplementary material available at 10.1186/s13063-024-08308-1.

## Background

Suicide is a serious public health issue, and men are at disproportionately high risk [1]. In most Western countries including Australia, Canada, the UK, and the US, men are nearly three times more likely than women to die by suicide [2, 3]. Some of the disparity in suicide rates between men and women may be attributed to men being less likely to seek help for suicidal thoughts and behaviours. Research indicates that, in the year preceding suicide, 58% of women had contacted mental health services, whereas only 35% of men had done so [4]. The low service engagement among men with suicidal thoughts or behaviour has been suggested to be related to high self-reliance, the absence of a formal mental health diagnosis, lack of interpersonal support, and past negative experiences with formal health services [5, 6]. Given that suicide is an irreversible tragedy with profound impacts on individuals and their families, it is crucial to develop new approaches that more effectively target men who are experiencing suicidal thoughts and/or behaviour but are not actively seeking or receiving support services. Here, we refer to this at-risk population as those who are ‘under the radar’ of support services.

Most of the research on interventions aimed at promoting formal mental health help-seeking has to date, focused on using psychoeducation or cognitive behavioural strategies to improve mental health literacy [7, 8], reduce stigma related to help-seeking [9], or enhance motivation to engage with services [10]. Face-to-face delivery has been by far the most widely used approach to implementing these interventions, with interventions typically delivered by health professionals, case managers, or other community-based practitioners [11]. Although meta-analyses show some evidence of statistically significant effects of these interventions on help-seeking intentions and behaviour, most trials use an inactive or no control condition, and for the few that do use an active control comparator, non-significant effects are observed [11]. Importantly, these interventions have predominantly focused on promoting help-seeking among individuals with mental health problems who are already in contact with a service. This represents a significant implementation barrier for promoting help-seeking among men with suicidal thoughts/behaviour since many do not have a formal mental health diagnosis and are not engaged with formal services [12]. Furthermore, few prior studies have assessed the effectiveness of help-seeking interventions that are designed to address the specific barriers that prevent men from engaging with formal support services. Accordingly, new approaches that are tailored towards the unique needs of men who are ‘under the radar’ are needed.

The Internet offers a unique platform for delivering a wide range of digital assistance, which is particularly beneficial for individuals who may hesitate to seek help in person due to concerns about privacy or logistical obstacles. Digital help encompasses various forms, including but not limited to the provision of health information, connection with supportive communities of others with shared experiences, triage services, as well as automated or blended therapeutic interventions [13]. Notably, web-based video messages have been found to be highly engaging compared to other content formats such as online images or posts when it comes to delivering health information [14]. However, the application of video messages in the field of suicide prevention is an area that requires further exploration and investigation.

## Objectives

The primary aim of the Under the Radar trial is to determine which of five promotional messages is most effective at encouraging men with suicidal thoughts, who are ‘under the radar’, to engage with online support services. Five web-based video messages have been developed and will be evaluated in a five-arm randomised controlled trial. Three of the video messages were developed based on themes derived from reviews of the literature [5], a survey of help-seeking in men at risk of suicide [12], and through qualitative interviews with men experiencing suicidal thoughts [15]. Accordingly, these videos reflect the personal experiences and key issues of concern for men who do not access help for their suicidal thoughts. Two control video messages were also created, which provide either generic help-seeking advice or statistics on suicide. We hypothesise that video messages tailored to the concerns and personal experiences of men who are under the radar will be more effective at promoting engagement with support services than either generic help-seeking messaging or to factual data around suicide deaths and attempts.

A secondary aim of this study is to understand what attributes of support services men with suicidal thoughts value most. We will assess these service preferences using the Discrete Choice Experiment (DCE) methodology, which is popular in the field of health economics [16, 17]. DCEs involve presenting individuals with pairs of hypothetical support services that vary on a set of attributes (e.g. cost) and attribute levels (e.g. high cost vs. free). Participants are asked to select which service out of each pair they prefer. Based on participants’ pattern of choices, the relative preferences for the different attributes and levels can be estimated. This methodology will provide us with critical insights into the service attributes that are most appealing to men who are experiencing suicidal thoughts, as well as attributes that may hinder men’s willingness to engage with a service.

Together, the findings from this study are expected to yield valuable insights into how to encourage help-seeking and provide better support for men who are experiencing suicidal thoughts. Additionally, the findings from the trial may serve as the foundation for a nationwide communication campaign aimed at preventing suicide in men and strengthening partnerships with organisations dedicated to suicide prevention.

## Methods

### Trial design and setting

This is a five-arm randomised controlled superiority trial with three active arms and two control arms. Participant recruitment, administration of study procedures, and data collection will be conducted entirely online. Once enrolled in the study, participants will be randomly assigned to view one of five video message interventions; three of which test evidence-based messaging derived from themes in the prior literature, and two control videos that promote general help-seeking and suicide awareness. After viewing the videos, participants will be presented with a directory containing information about four mental health support services available in Australia, which have been selected for inclusion in this study based on their specialisation in providing mental health support for men, for their national reach, and for their range of service offerings (e.g. online help, telephone support, etc.). The four services are MensLine Australia, Mosh, Roses in the Ocean, and SANE Australia. Participants will be invited to click on a link to one or more of these services to find out more about what the service offers. There are three measurement occasions during the trial: baseline, post-intervention (immediately after viewing the video), and a 1-week follow-up (see Fig. 1).

**Fig. 1 Fig1:**
[figure not shown]
Trial flow

### Patient and public involvement statement

A group of men with experience of suicidal thoughts, past history of trauma, and hesitancy against seeking help from formal mental health services participated in workshops and design exercises during the initial planning phase of this study. These men provided perspectives on the needs and views of those ‘under the radar’. Some of these men were also involved in quantitative and qualitative studies that were conducted prior to, and which informed, the design of the current study. All men were supported by the Black Dog Institute’s lived experience team and were paid for their participation.

### Sample and recruitment

A total of 380 men who are experiencing suicidal thoughts and who are not in receipt of formal mental health care will be recruited for this trial. Recruitment will be done using a social media drive involving advertisements posted on Facebook, Twitter, and Instagram. This recruitment strategy has proven successful in reaching our target population in prior survey and qualitative interview studies that were conducted during earlier phases of this project [12]. This initial contact will involve minimal real or perceived coercion or pressure to participate as the research team will not have direct contact with potential participants. Recruitment for the trial started on the 24th of July 2023. Participants will be reimbursed for their participation by means of two $20 GiftPay vouchers (total of $40)—one for completing the post-study survey and one for completing the follow-up survey. The reimbursement is being offered in acknowledgement of participants’ time and effort spent on completing the surveys and viewing the study intervention (video message). The gift vouchers will be provided to participants via the email address they provided after they were deemed eligible to participate in the study.

### Eligibility and screening

Participants will be eligible to participate if they (1) identify as a man, (2) are fluent in English, (3) are currently living in Australia, (4) have had thoughts of dying or hurting themselves in the past 6 months, and (5) have not accessed formal mental health services (including counsellors, general practitioners, psychologists, psychiatrists, and other mental health professionals) in the past 6 months.

Screening will be conducted online. First, participants who are interested in taking part in the study will click on a link in the recruitment advertisements. This link will take them to a study landing page where they will have the opportunity to read more about the study, view the participant information statement and consent form, and register to take part in the trial. After providing online consent, participants will answer a brief online screening survey to assess their eligibility. Those who are deemed eligible will continue on to the baseline questionnaire. Once participants enrol into the study, they are permitted to engage in any form of treatment they wish.

### Random allocation and blinding

Randomisation to the five trial arms will be conducted on a 1:1:1:1:1 ratio using a computerised algorithm. A blocked approach to randomisation will be implemented (block size of 10), using age as a stratifying variable (three stratums: age 18 to 35; age 36 to 64; age 65 or older). Participants will be randomised after consent has been provided and eligibility has been confirmed.

Participants will not be informed about the condition (intervention or control) to which they are assigned. The chance that participants will discern their condition assignment is low as the intervention and control video messages are presented in the same format. Operational staff involved in day-to-day participant management will be unblinded because the nature of the interventions requires that they cannot easily be concealed. All other investigators will be blinded to intervention assignment throughout the study period.

### Active conditions: videos portraying themes derived from studies on barriers to help-seeking for men with suicidal thoughts

The three key video messaging interventions will portray content as follows: (1) one video emphasises the positive elements of masculinity and conveys the message that seeking help requires strength, rather than constituting a weakness; (2) a second video challenges the idea that self-reliance is the best way to manage suicidal thoughts, and articulates how help-seeking facilitates problem-solving and development of practical solutions; and (3) a third video acknowledges that prior negative experiences with support services can act as a barrier to reaching out for help again, but emphasises the potential benefits to be gained by trialling services to find one that works.

The themes and content of the video messages were designed based on the quantitative and qualitative findings from earlier phases of the project [5, 12, 15, 18–21]. The video messages were of high-quality production and created by an award-winning filmmaker. Each video is approximately 2 min in length and is centred around a Caucasian, middle-aged male actor, who portrays first-hand experience of having suicidal thoughts. All videos are set in a domestic environment and depict the actor performing everyday tasks (e.g. making a cup of coffee, using tools to fix a skateboard) while speaking to the camera. Each video message ends with the actor encouraging the viewer to consider the support options provided. The actor’s age and ethnicity were chosen to match the demographic characteristics of our target population (in Australia, the largest number of men to die by suicide are Caucasian and aged 25–44 years).

### Control conditions: videos portraying generic messages around help-seeking and suicide awareness

The two control video messages portray the following content: (1) one video uses messaging similar to that used on the websites of existing suicide prevention organisations, and promotes help-seeking and general awareness of the availability of support services for individuals experiencing suicidal thoughts; (2) a second video aims to increase the viewers’ general knowledge of the prevalence of suicide in Australia by presenting Australian suicide statistics in the style of a news presenter. These two control video messages are of the same length as the active intervention video messages and are presented in the same style and with the same actor.

### Assessment schedule

Outcomes will be collected at three time points: baseline (day 1), post-intervention (day 1), and 1-week follow-up (day 8). Data collection will be conducted entirely online through an automated trial platform. Immediately following completion of the screening survey, eligible participants will complete the baseline questionnaires, view the video messaging intervention, and complete the post-intervention questionnaires. One week later, participants will receive an SMS prompt inviting them to complete the 1-week follow-up questionnaires. Participants have a maximum of 72 h to complete baseline and post-intervention, and another 72 h to complete follow-up. The DCE survey is available for the duration of the trial. See Fig. 2 for the trial timing where participant A completes all tasks at the first opportunity, while participant B uses all of the grace period before completing the tasks.

**Fig. 2 Fig2:**
[figure not shown]
Trial timing

During the baseline assessment, only a small number of questionnaires will be administered. This approach aims to minimise the impact of pre-exposure to information on the type of support that is sought. A minimal baseline questionnaire battery also more closely replicates the conditions of mass media campaigns, where individuals approach the content with limited prior knowledge of what the campaign is about.

### Outcome measures

The full schedule of assessments is shown in Table 1.

**Table 1 Tab1:** Summary of the primary, secondary, other outcome measures, and data collection time points

Outcome measures	Assessment	Baseline	Post-intervention	One-week follow-up
*Primary outcome*				
Help-seeking behaviour	Click-throughs	–	✓	–
*Secondary outcomes*				
Use of support services	Self-report item	–	–	✓
Help-seeking intentions	Self-report item	–	–	✓
Service preferences	Discrete Choice Experiment	–	✓	–
*Exploratory outcomes*				
Awareness of services	Self-report item	–	✓	–
Frequency of services chosen	Click-throughs	–	✓	–
Intervention acceptability	Theoretical Framework of Acceptability Questionnaire	–	✓	–
Time spent viewing video	Seconds of video play	–	✓^a^	–
Suicidal distress	University of Washington Risk Assessment Protocol	✓	✓	–
Demographics	Self-report item	✓	–	–
Suicidal thoughts	Suicidal Ideation Attributes Scale	–	✓	–
General mental wellbeing	Short Warwick Edinburgh Mental Wellbeing Scale	–	✓	–
Psychological distress	Kessler Psychological Distress Scale	–	✓	–
Loneliness	Three-Item Loneliness Scale	–	✓	–
Anhedonia	Snaith-Hamilton Pleasure Scale	–	✓	–
Physical and mental health	Self-report item	–	✓	–
Barriers to services	Barriers to Access to Care Evaluation Scale	–	–	✓
*Process outcomes*				
Service engagement patterns	Service usage data provided by four support services	–	–	✓

^a^Measured during intervention delivery

#### Primary outcome

##### Help-seeking behaviour

The primary outcome is help-seeking behaviour, operationalised as a click on the link to at least one of the four support services presented to participants (i.e. MensLine Australia, Mosh, Roses in the Ocean, SANE Australia) immediately after the video is shown.

#### Secondary outcomes

##### Use of support services

Use of the four support services will be assessed at the 1-week follow-up using a single item that asks participants whether they have used any of the four support services in the past week (response options: ‘Yes’ or ‘No’).

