##### Prior awareness and use of the four support services

Participants’ awareness and use of the four support services prior to the study will be assessed using two closed-choice questions presented at the post-intervention assessment: (1) ‘Have you heard of any of the following services (MensLine Australia, Mosh, Roses in the Ocean and SANE Australia) before taking part in this study?’ and (2) ‘Have you used any of the following services (MensLine Australia, Mosh, Roses in the Ocean and SANE Australia) before taking part in this study?’ Response options: ‘Yes’ or ‘No’.

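### The 1-week service-use outcome cannot separate use prompted by the video from use already under way, and the entry criterion leaves open whether some continuing users of the four services can enrol

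*Protocol article*

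**What the plan says.** **Outcome.** Under 'Use of support services', the protocol asks men at 1 week "whether they have used any of the four support services in the past week", answered Yes or No. The item does not distinguish first, resumed and continuing use.

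**Analysis.** 'Analysis of secondary outcomes' applies the primary-outcome approach. Those logistic models contain only terms for the videos: one pooled contrast of tailored against control, and two terms comparing the tailored videos.

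**Entry.** Under 'Eligibility and screening', criterion 5 requires that men "have not accessed formal mental health services (including counsellors, general practitioners, psychologists, psychiatrists, and other mental health professionals) in the past 6 months". The four study services are not named there.

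**The four services.** 'Trial design and setting' describes "a directory containing information about four mental health support services available in Australia", chosen among other things "for their range of service offerings (e.g. online help, telephone support, etc".

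**Prior use.** An exploratory item, given after the video, asks: "Have you used any of the following services (MensLine Australia, Mosh, Roses in the Ocean and SANE Australia) before taking part in this study". It has no time window, and the analysis sections do not link it to the 1-week outcome.

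**Target population.** The Background describes men who are "not actively seeking or receiving support services".

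**The concern.** The trial asks whether a message moves men who are outside the support system to use a service. A man who was already using online help from one of the four services, and continues, answers 'Yes' whichever video he saw. His answer says nothing about the video, but it is counted as an event.

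The primary outcome is a click on a link. The data supplied by the services are pooled across all arms ('Patterns of service engagement'). The 1-week item is therefore the only measure of actual service use that is available for each man and by arm. If part of its event count is use already under way, two things suffer: the estimated odds ratio moves toward 1, and the percentage of men who used a service overstates uptake if it is read as uptake.

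**Working it through.** **Step 1: can a continuing user be in the sample?** Set the passages side by side.

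- Criterion 5 turns on the word formal and illustrates it with counsellors, general practitioners, psychologists, psychiatrists and other mental health professionals. A man seen by such a person at one of the four services in the past 6 months is excluded.
- The four services also offer online help. The protocol does not say whether using that kind of help counts as formal care.
- The prior-use item covers any use before the study. A 'Yes' may come from a man who stopped years ago, so the item allows for prior users but does not show that current users enrol.

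So the gap is limited to current contact that might be judged not formal. For those men entry is unclear, and the 1-week item and its models would not separate them.

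**Step 2: what would a given share do?** The protocol gives no expected rate and no power figure for this outcome, so there is nothing of its own to reproduce. What follows is illustration.

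Inputs:
- Group sizes from the protocol: 3 × 76 = 228 tailored, 2 × 76 = 152 control. Complete follow-up is assumed.
- New-use rates p: 10% tailored, 4% control (assumed).
- Share c of continuing users, equal in all arms because of randomisation, all answering 'Yes' (assumed).

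Formulas:
- Observed rate P = c + (1 − c)p.
- Odds ratio = [P1/(1 − P1)] / [P0/(1 − P0)].
- Share of control 'Yes' answers that are continuing use = c/P0.
- Power = Φ[(P1 − P0 − 1.96·SE0)/SE1], two-sided 5%. SE0 uses the pooled rate and SE1 the separate rates.

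Example, c = 5%: P1 = 0.05 + 0.95 × 0.10 = 0.145 and P0 = 0.05 + 0.95 × 0.04 = 0.088. Odds ratio = (0.145/0.855)/(0.088/0.912) = 1.76. SE0 = 0.0343 and SE1 = 0.0327, so power = Φ[(0.057 − 0.0672)/0.0327] = 38%.

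| c | Tailored | Control | Risk difference (points) | Odds ratio | Power | Control 'Yes' that is continuing use |
|---|---|---|---|---|---|---|
| 0 | 10.0% | 4.0% | 6.0 | 2.67 | 59% | 0 |
| 2% | 11.8% | 5.9% | 5.9 | 2.13 | 48% | 34% |
| 5% | 14.5% | 8.8% | 5.7 | 1.76 | 38% | 57% |
| 10% | 19.0% | 13.6% | 5.4 | 1.49 | 27% | 74% |

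**Step 3: how far does this depend on the assumed rates?** Borrowing the protocol's click rates, 28% v 8% (also an assumption for this outcome), c = 0, 5% and 10% give odds ratios of 4.47, 3.20 and 2.61, and power of 0.999, 0.994 and 0.977. With 10% v 3%, power is 0.76, 0.50 and 0.36. The loss of power is serious only if true new use is uncommon. The risk difference shrinks by the factor 1 − c in every case.

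**The case against.** **Entry does screen men out.** A reader might infer that nothing at entry stops current users of the four services from enrolling. The documents do not support that. Criterion 5 excludes recent contact with counsellors and other professionals, and 'Patterns of service engagement' gives sessions with a psychologist as an example of what the services may report. Men in that kind of contact are ineligible. This objection stands, and it narrows the point to non-clinical contact.

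**Prior use is not continuing use.** A reader might also take the prior-use question as proof that continuing users are in the sample. It asks about any past use, so it proves no such thing. This stands too.

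**The stated outcome is use, not new use.** The abstract and the outcome section agree on this. Returning after a lapse is an intended effect, since the third tailored video addresses men put off by earlier bad experiences. This stands, and it argues against redefining the outcome. A new response list that separates first use from earlier use would also misplace the lapsed man who returns, and it would create two item versions in a trial recruiting since July 2023.

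**Covariates belong in the SAP.** This has some force, because the SAP is not shown. However, the article does fix the analysis as the same models as for the primary outcome, and the wording of criterion 5 is a protocol matter. Since the needed item is already collected, stating its use costs almost nothing.

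**Conclusion.** The point holds in a limited form. Criterion 5 leaves it unclear whether non-clinical contact with the four services disqualifies a man. If such men enrol, their continuing use is scored as though the video had prompted it, and the stated models contain nothing to separate the two.

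The expected consequence is an odds ratio closer to 1, some loss of power and an overstated uptake figure. A reader might infer that the comparison is biased in favour of one arm. It is not: randomisation makes the share of continuing users equal across arms in expectation.

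The number of men affected is not given and may be small. The illustrated fall in odds ratio from 2.67 to 1.76 rests on assumed new-use rates, an assumed 5% share, and every continuing user answering 'Yes' in that one week. The risk difference barely moves. This is a modest weakness in a secondary outcome and does not touch the primary analysis.

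**What to change.** 1. Keep any use in the past week as the stated outcome, and leave the item and its response options unchanged.
2. In 'Analysis of secondary outcomes', prespecify an analysis of 1-week use that adjusts for prior use of the four services, taken from the existing exploratory item. The item follows the video but asks about history before the study, which the video cannot alter.
3. Add a sensitivity analysis in men who report no prior use, and report 1-week use by arm separately for men with and without prior use.
4. State the limit of that item. It records any past use, so the restricted analysis also drops lapsed users who return, some of whom the third video is meant to reach. It is therefore supportive only.
5. State in criterion 5 whether contact with the four study services, including online help, counts as formal care. For men already enrolled, say how the criterion was applied.

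The cost is one or two extra analyses, somewhat fewer events in the restricted set, and one clarifying sentence. No new data are needed.

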#### Analysis of secondary outcomes

Use of the four services within the 1-week follow-up period will be analysed using the same approach as used for the primary outcome. Help-seeking intentions, which are measured on a 7-point Likert scale, will be measured using ordinal logistic regression. In the case that some levels on this 7-point scale are underrepresented, we will consider combining adjacent categories as appropriate.

We will analyse respondents’ choices made within the DCE by estimating the conditional logit models [31] and mixed logit models [32]. These analyses will be performed using STATA (version 18). These models can be interpreted via the Random Utility Theory which assumes that individuals will choose the alternative that provides them with the highest utility. We will also estimate the Willingness to Pay (WTP), which is the dollar amount individuals are willing to pay for service changes. Relative importance of attributes will also be assessed to understand the relative impact that an attribute has on choice. For example, the preference analysis results will allow us to explore whether men prefer one service type (e.g. peer support) over another (e.g. seeing a psychiatrist). The WTP results will indicate the dollar amount men are willing to pay to receive one service compared to another (e.g. they might be willing to pay $50 more to receive services individually rather than in a group setting). The relative importance results will allow us to understand the ranking of the suicide prevention attributes (e.g. the most important factor affecting choice may be service type, followed by waiting time, cost, etc.). To explore observed heterogeneity, sub-group analyses will be undertaken by interacting the preference weights with a range of socio-demographic characteristics including age, educational attainment, employment status, income levels, etc. This will allow us to understand why individuals in one sub-group (e.g. higher educational attainment) may have different preferences compared to those in another sub-group (e.g. lower educational attainment).

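### The service-use item looks back one week from the day of answering, so for men who respond late it can miss up to the first three days after the video

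*Protocol article*

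**What the plan says.** Under Use of support services, the protocol article describes a single Yes/No item, given at the one-week follow-up, which asks participants "whether they have used any of the four support services in the past week".

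The outcome itself is described by reference to the follow-up period. The abstract calls it "self-reported use of the support services during a 1-week follow-up period", and Analysis of secondary outcomes states: "Use of the four services within the 1-week follow-up period will be analysed using the same approach as used for the primary outcome".

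Assessment schedule places the video and post-intervention survey on day 1 and the follow-up on day 8. It then says: "One week later, participants will receive an SMS prompt inviting them to complete the 1-week follow-up questionnaires". It adds: "Participants have a maximum of 72 h to complete baseline and post-intervention, and another 72 h to complete follow-up". Late completion is expected, since the text introducing Fig. 2 describes a case in which "participant B uses all of the grace period before completing the tasks". Nothing in the article ties the recall period to the date of the video or adjusts it for a late answer.

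**The concern.** Two different weeks are in play. The outcome refers to the week that starts with the video. The item refers to the week that ends with the answer. They coincide only if the answer is given exactly seven days after the video, and the schedule permits later answers. For a late responder, the days that drop out are the first ones after the video and the service links were shown. A man who contacted a service only in those days could correctly answer No.

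The item carries some weight. Under Patterns of service engagement, the data supplied by the services come pooled over all arms, and the primary outcome is a click on a link. This item is therefore the only measure of actual service use that can be compared between arms, and the pooled service data cannot repair it by arm. Use that was never asked about cannot be recovered in analysis.

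**Working it through.** **Inputs (protocol article).** Video and post-intervention survey on day 1, follow-up on day 8, prompt one week later, 72 h to complete each stage (Assessment schedule). Recall period of one week (Use of support services).

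**The plan's own figure.** Day 8 − day 1 = 7 days, so a man who does everything at once answers seven days after the video. His recall window is exactly the follow-up week and he loses nothing.

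**Prompt timed from the video (the plain reading).** Let g be the delay in days between prompt and answer, from 0 to 72/24 = 3.

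- Time of answer after the video = 7 + g, so 7 to 10 days.
- Start of recall window = (7 + g) − 7 = g days after the video.
- Days of the follow-up week left out = g; share left out = g/7.

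| Delay after prompt | Answer, days after video | Days left out | Share of first 7 days |
|---|---|---|---|
| 0 h | 7 | 0 | 0% |
| 24 h | 8 | 1 | 14% |
| 48 h | 9 | 2 | 29% |
| 72 h | 10 | 3 | 43% |

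The window shifts rather than shrinks. It also reaches g days beyond day 7 after the video, so first use in that stretch would count although it lies outside the follow-up week.

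**Other starting points for the one-week interval.** The text does not state the starting point outright, and Fig. 2 is not reproduced.

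- Timed from completion of the post-intervention survey, with the video seen at the start of the first 72 h and the survey finished at the end: 3 + 7 + 3 = 13 days after the video at the latest, so up to 13 − 7 = 6 days left out.
- Timed from enrolment: the answer falls between 7 − 3 = 4 and 7 + 3 = 10 days after the video. The window can then include up to 3 days before the video or leave out up to 3 days after it. A man who uses both grace periods in full sees the video at 72 h and answers at 168 + 72 = 240 h. His look-back starts at 240 − 168 = 72 h, so he has no mismatch.

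**Effect on the arm contrast (illustration only).** Suppose 20% of true users are lost equally in both groups and there are no false Yes answers. The 28% and 8% click rates from Sample size and power are borrowed purely as example values.

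- Recorded proportions: 0.28 × 0.8 = 22.4% and 0.08 × 0.8 = 6.4%.
- Risk difference: 20.0 points falls to 16.0 points.
- Risk ratio: 28/8 = 3.5 and 22.4/6.4 = 3.5, unchanged.
- Odds ratio: (0.28/0.72)/(0.08/0.92) = 4.47 falls to (0.224/0.776)/(0.064/0.936) = 4.22.

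Equal loss costs events and shrinks the risk difference, but barely moves the odds ratio, which is the planned logistic measure.

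**The case against.** - **Prompt responders lose nothing.** The gap exists only for late answers, and the article gives no share of these. This stands.
- **The item is paraphrased.** The article reports it in indirect speech, and the displayed question could carry a date or anchor. This stands as a caveat, but the article as written gives a one-week look-back and no anchor.
- **People may not apply an exact cut-off.** A man might count a contact eight days ago as the past week, and anyone who used a service both early and later still answers Yes. Both points reduce the loss without removing it.
- **It is a secondary outcome.** The primary click outcome is recorded straight after the video and is unaffected. This stands.
- **Rewording mid-trial puts two instruments into one outcome.** This is a real but small cost, handled by a flag.

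Three stronger readings are tempting and not supported. First, a reader might infer that early use is missed in general, or that the first days are when prompted contact is most likely. The schedule limits the gap to late responders, and the article has no information on when contact happens. Second, a reader might put a size on the loss. Assuming that 50% of users acted only in the first 24 h and 40% of men answer more than 24 h after the prompt gives 0.5 × 0.4 = 20%; 30% × 20% gives 6% and 60% × 60% gives 36%. None of these inputs comes from the article. Third, a reader might conclude that pre-video use contaminates the item. That depends on timing from enrolment, which cannot be settled without Fig. 2, and even then only some combinations of delay produce it. The directory of services is also shown only after the video.

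**Conclusion.** The mismatch between recall period and outcome period is real on the article's own text. If the prompt is timed from the video, up to the first 3 of 7 days fall outside the window for men who use the full 72 h, and none for men who answer when prompted. Early-only use can therefore be missed for late responders.

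The size of the under-count is unknown, because neither the share of late responders nor the timing of use is given. The expected effect is fewer recorded events, some loss of power and a smaller risk difference. This assumes that the days gained after day 7 do not make up for those lost. A reader might infer that the arm comparison is clearly diluted or biased. With equal loss in all arms the odds ratio moves only slightly. Material bias needs response delay or the share of early-only use to differ by arm. The latter is conceivable if the target videos prompt more immediate action, but nothing in the article shows it.

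The point is worth correcting because this is the only arm-level measure of actual service use. It does not touch the primary outcome.

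**What to change.** - **Anchor the item to the video.** For example: *Since you watched the video on [date filled in by the platform], have you used any of these services?* This leaves no post-video day outside the window.
- **Ask the date of first use, and define the outcome as use within seven days of the video.** Without the date, the anchored item would cover 7 to 10 days depending on when the man answers (prompt timed from the video).
- **State the starting point of the one-week interval** in the text as well as in Fig. 2.
- **Record which wording each man received.** Recruitment began in July 2023, so both versions may be present.
- **For answers already collected, report logged response delay by arm.** An analysis restricted to men who answered within 24 h of the prompt can be added, but only as supportive, because that subset is selected after randomisation.

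The cost is one reworded item with a date field, a minor ethics amendment and a wording flag in the data set.
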